#### In-home/telephone follow-up only intervention group (Group 4)

Patients allocated to the in-home/telephone follow-up only intervention group

will receive only the APGN component of the protocol, that is, protocol steps 1, 2, 5, 6, 7, 9, 10, and 11.

### Data quality assurance

All completed patient questionnaires are checked for errors and missing data by a SRA as they are returned. Data entry will be double checked against the paper-based questionnaires. Inconsistencies in data entry will be corrected by referring back to the paper-based version of the questionnaire or medical records as appropriate.

### Intervention integrity

The study is guided by the CONSORT (Consolidated Standards of Reporting Trials) statement [21]. Participants will be randomly allocated into one of the four study trial groups after baseline assessment and data collection. Blinding of research staff collecting participant outcomes data will occur. The intervention protocol is documented and all data collected is stored in the study database. Data entry will be double checked against the paper-based versions of the questionnaires. All data analyses will be conducted based on the principle of intention to treat [22].

### Study outcomes

#### Primary outcomes

Primary outcomes include emergency health service use (i.e. unplanned readmissions, time to first unplanned readmission, unplanned Emergency Department, General Practitioner and other health service use), and functional ability (Instrumental Activities of Daily Living [23], Index of Activities of Daily Living [24], Walking Impairment Questionnaire [25]).

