**Methods/Design:**

The study is a randomised controlled trial. Within 72 hours of hospital admission, a sample of older adults fitting the inclusion/exclusion criteria (aged 65 years and over, admitted with a medical diagnosis, able to walk independently for 3 meters, and at least one risk factor for readmission) are randomised into one of four groups: 1) the usual care control group, 2) the exercise and in-home/telephone follow-up intervention group, 3) the exercise only intervention group, or 4) the in-home/telephone follow-up only intervention group. The usual care control group receive usual discharge planning provided by the health service. In addition to usual care, the exercise and in-home/telephone follow-up intervention group receive an intervention consisting of a tailored exercise program, in-home visit and 24 week telephone follow-up by a gerontic nurse. The exercise only and in-home/telephone follow-up only intervention groups, in addition to usual care receive only the exercise or gerontic nurse components of the intervention respectively. Data collection is undertaken at baseline within 72 hours of hospital admission, 4 weeks following hospital discharge, 12 weeks following hospital discharge, and 24 weeks following hospital discharge. Outcome assessors are blinded to group allocation. Primary outcomes are emergency hospital readmissions and health service use, functional status, psychosocial well-being and cost effectiveness.

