### Trial aims

The overall aim of this trial is to evaluate the relative effectiveness of transitional care strategies commencing during hospitalisation for community-based high risk older adults on emergency readmissions and health service use, functional ability and quality of life outcomes. Specifically, the aims are to:

1. Conduct a randomised control trial to compare and evaluate transitional care interventions targeting older patients aged over 65 years who are at risk of hospital readmission after discharge;

2. Compare and evaluate innovative exercise and telephone follow-up interventions following discharge in comparison to usual care, on primary and secondary outcomes at 4 weeks, 12 weeks, and 24 weeks. Primary outcomes include emergency health service use (i.e. unplanned readmissions, time to first unplanned readmission, unplanned Emergency Department, General Practitioner and other health service use), and functional ability. Secondary outcomes include health-related quality of life, psychosocial well-being, and cost effectiveness; and

3. Apply the RE-AIM evaluation framework [20] which uses Reach, Effectiveness, Adoption, Implementation, and Maintenance to assist in understanding the various factors which impact upon the intervention becoming a routine part of the usual care provided by a health service.

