#### Sample size

A total of 328 participants (82/group) is aimed to be recruited. Based on our previous research in the area [19] it is anticipated that there will be approximately 25% attrition (20/group) over 6 months of follow-up for reasons such as death, changing mind about participating, or moving away. A sample of 62 completing participants per group (82-20 = 62) is required to detect a 4 week difference in time to hospital readmission. This sample size was determined by power analysis and based on an expected difference in median time to readmission between groups over 24 weeks. Significance level (alpha) was established at 0.05 to avoid a Type 1 error, and power (1 - beta) was set at 90% to avoid a Type II error. Therefore, for a 90% chance of detecting as significant a 4 week difference in time to hospital re-admission, 62 patients in each group are needed to complete the study.

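### The abstract and body disagree on which outcomes are primary, and the body names eight unranked primary measures although the trial is sized on only one

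*Protocol article*

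**What the plan says.** The abstract (Methods/Design) states: "Primary outcomes are emergency hospital readmissions and health service use, functional status, psychosocial well-being and cost effectiveness".

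The Trial aims section states: "Secondary outcomes include health-related quality of life, psychosocial well-being, and cost effectiveness". The Secondary outcomes section agrees with the aims and again places psychosocial well-being and cost effectiveness among the secondary outcomes.

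The Primary outcomes section gives two groups of measures:

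- Service use: "unplanned readmissions, time to first unplanned readmission, unplanned Emergency Department, General Practitioner and other health service use". Counting the last item as one, that is five measures.
- Functional ability: three instruments (instrumental ADL, the ADL index and the Walking Impairment Questionnaire).

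That makes eight primary measures, with no order among them.

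The Sample size section uses one quantity only. The calculation is "based on an expected difference in median time to readmission between groups over 24 weeks", for a 4-week difference. Alpha is given once: "Significance level (alpha) was established at 0.05 to avoid a Type 1 error". The stated power is 90%. The result is that "62 patients in each group are needed to complete the study".

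The Trial aims and Discussion compare three interventions with usual care.

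**The concern.** Two current statements in the same article give different primary outcomes. No later analysis plan can make both true; one has to be corrected. Interventions and data collection were already under way when the article was written (Background), so the article serves as the public record of what was prespecified. A reader could cite either list once results are known.

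The body's own list also leaves the lead outcome open. Eight measures have equal standing, and the only one that resembles the sizing outcome is not singled out. A favourable result on any of the eight could be presented as a primary finding, while the stated 90% power refers to only one of them. Which outcome leads is a protocol decision, not a detail usually left to a statistical analysis plan.

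**Working it through.** **1. The two lists side by side**

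| Outcome | Abstract | Trial aims and outcomes sections |
|---|---|---|
| Readmissions and health service use | primary | primary |
| Functional status or ability | primary | primary |
| Psychosocial well-being | primary | secondary |
| Cost effectiveness | primary | secondary |

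The conflict is confined to the last two rows. The body agrees with itself.

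**2. The plan's own figures**

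The arithmetic in the Sample size section holds: 82 − 20 = 62 and 4 × 82 = 328. Dividing by the retention rate gives 62 / 0.75 = 82.7, so 83 against the stated 82, a trivial difference.

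The 62 itself can be neither reproduced nor refuted, because neither median is given. Under exponential survival (an assumption) it fits a control median near 5 weeks. For 5 against 9 weeks the hazard ratio is 5/9 = 0.556. Schoenfeld's formula, two-sided, gives 4 × (1.960 + 1.282)² / (ln 0.556)² ≈ 122 events. That is 61 per group without censoring, or 68 per group with censoring at 24 weeks. The 62 is taken as correct below.

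**3. Chance of at least one false positive, if every measure were tested at 0.05**

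Inputs: eight measures (Primary outcomes), three interventions against one control (Trial aims, Discussion), equal groups and alpha 0.05 (Sample size). Assumptions: two-sided tests, since sidedness is not stated, and one common correlation between outcomes, which the documents do not give.

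- Eight independent measures, one comparison: 1 − 0.95⁸ = 33.7%.
- One measure, three independent comparisons: 1 − 0.95³ = 14.3%. With the shared control (simulation, 400,000 replicates) it is 12.5%.
- Eight measures, with the shared control included in the three-comparison column (same simulation):

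| Assumed outcome correlation | One comparison | Three comparisons |
|---|---|---|
| 0 | 33.7% | 65.7% |
| 0.3 | 30.0% | 60.6% |
| 0.5 | 25.0% | 52.7% |
| 0.7 | 19.0% | 42.0% |
| 0.9 | 12.0% | 27.7% |

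**4. Power if one primary outcome were adjusted for three comparisons**

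At a two-sided 0.05 and 90% power, the expected test statistic is 1.960 + 1.282 = 3.242.

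- Dunnett critical value 2.348 (two-sided alpha about 0.0189): 3.242 − 2.348 = 0.894, power about 81%.
- Bonferroni alpha 0.05 / 3 = 0.0167, critical value 2.394: 3.242 − 2.394 = 0.848, power about 80%.
- Restoring 90% under Bonferroni: [(2.394 + 1.282) / 3.242]² = 1.286, and 62 × 1.286 = 79.7, so 80 completers per group. With 25% attrition, 80 / 0.75 gives 107 per group, 428 in total, against the stated aim: "A total of 328 participants (82/group) is aimed to be recruited".

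**The case against.** A reader might infer that the protocol tests every measure, in each pairwise comparison with control, at an unadjusted 0.05, so that Type I error is uncontrolled. The document does not say so. The 0.05 appears once, as an input to the power calculation for time to readmission. No success rule is stated, and a multiplicity procedure is commonly left to the analysis plan, which is not at hand. The absence of one from a condensed article is not an error.

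A reader might also multiply the tests by the three follow-up visits. The Data analysis section does not support this for the main measures. It plans survival methods for service use and a repeated-measures model across all data collection points for continuous outcomes such as functional status. It also names chi-square, ANOVA and Kruskal-Wallis tests, which could serve as four-group global tests and so reduce the multiplicity from the arms.

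Whether distinct interventions against one control need adjustment at all is debated. High correlation is plausible for some pairs: readmissions and time to first readmission come from the same events, and the two ADL scales are related. Finally, the body is consistent, so the labelling conflict is a one-line correction to the abstract.

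All of this stands, and it limits what can be claimed about error rates. It does not remove the conflict between abstract and body, or the lack of a lead outcome among eight. A global test first would still leave one test for each of eight outcomes, up to 33.7% if they were independent.

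**Conclusion.** The point holds in two parts that rest on the text itself. The abstract contradicts the body on psychosocial well-being and cost effectiveness. The body's primary set is eight unranked measures, while alpha, power and sample size are stated for one outcome that is never named as leading.

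The size is conditional on each measure being tested at 0.05 without adjustment, two-sided. It is then up to about 34% for a single comparison with independent outcomes, and about 28% to 66% for three comparisons with a shared control, at correlations from 0.9 to 0. These rates show what is at stake if no lead outcome is named. They do not describe a rule that the article states.

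**What to change.** Correct the abstract so that its primary outcomes match the Trial aims and the two outcomes sections.

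Name time to first unplanned readmission within 24 weeks as the single primary outcome. It is the listed measure closest to the sizing outcome, which the Sample size section calls only time to hospital readmission; that wording should be aligned. Make the remaining service-use and functional measures secondary, or place them below it in a stated hierarchy. Record the change before the data are analysed.

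The cost is a short amendment and no new data. Functional ability, which the Trial aims now list as primary, would lose equal standing; a hierarchy keeps it formally testable.

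Adjustment across the three intervention-versus-control comparisons (Dunnett, Holm or a fixed order) is optional, and the choice should be stated. It is not free. Taking 62 per group as correct, the nominal 90% power should be restated as about 81% with Dunnett or about 80% with Bonferroni. The Type II error then nearly doubles, from 10% to 19% or 20%. Restoring 90% under Bonferroni would need about 428 enrolled instead of 328.

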#### Secondary outcomes

Secondary outcomes include health-related quality of life (Short Form-12^v2 ^Survey [26]), psychosocial well-being (Geriatric Depression Scale [27], MOS Social Support Survey [28]), satisfaction with health care, and cost effectiveness (i.e., calculating the number of readmissions avoided, estimating time gained by delaying or preventing time to first re-admission, calculating mean treatment cost differentials between control and intervention groups).

#### Intervention Implementation

Adherence to the program is assessed and recorded during each follow-up implementation visits and/or telephone follow-up calls, including patients' exercise adherence and motivation.

#### Socio-demographic Information

Self-reported socio-demographic factors include age (in years), sex (male or female), ethnicity (born in Australia or overseas), education (attendance at secondary school or greater, employment status (currently employed or not), income levels (annual income <$30 K, $30-60 K or >$60 K), living arrangements (live with relative/friend, or spouse or live alone), and hospital insurance status (Medicare, private insurance, or Department of Veteran Affairs).

### Data analysis

#### Descriptive analysis

Baseline data from the control and intervention groups will be compared to check for comparability of the groups. Chi square tests will be used for categorical variables, ANOVA for normally distributed continuous variables, and Kruskal-Wallis tests for non-parametric data. Differences detected will be controlled for during the subsequent analyses.

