#### Inclusion criteria

The inclusion and exclusion criteria reflect patients who are at high risk of hospital readmission after hospital discharge (see [19] for a detailed account of previously published research identifying risk factors for readmission). Participants are included in the trial if the following criteria are met:

• aged 65 years and over,

• admitted with a medical diagnosis (i.e. non-surgical),

• able to speak and understand English, and

• have at least one of the following risk factors for readmissions: - aged 75 years or older,

- hospital admission/s in the previous 6 months to this admission,

- multiple comorbidities (2 or more),

- lives alone,

- lacks social support,

- fair or poor self-rating of health,

- moderate to severe functional impairment, and/or

- history of depression.

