#### Primary and secondary analysis

All data analyses will be conducted based on the principle of intention to treat [22]. Chi square, ANOVA, and Kruskal-Wallis tests will be used for bivariate analysis. For the primary outcomes of emergency health service use, Kaplan-Meier survival curves and log rank statistic will be used to compare intervention and control groups. A Cox proportional hazards regression model will be used to determine the effect of the interventions and adjust for any potential confounding variables. A general linear model approach will be used for multivariable repeated measures analysis of covariance for continuous outcome variables (e.g. measures of functional status, quality of life and psycho-social well-being) to investigate the differences over the four data collection points. Economic data will be collected to enable a comprehensive evaluation of the cost-effectiveness of the interventions when compared to that of usual care. Mean treatment costs differentials between control and intervention groups will be calculated. The patient level data will be used alongside other routinely available data to inform a decision analytic cost-effectiveness model.

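### Adjustment covariates are chosen by baseline significance tests, which under randomisation selects by chance and forgoes power, most clearly in the Cox analysis of time to readmission

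*Protocol article*

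**What the plan says.** The Descriptive analysis section of the protocol article states that "Baseline data from the control and intervention groups will be compared to check for comparability of the groups". The comparison is made by significance tests: "Chi square tests will be used for categorical variables, ANOVA for normally distributed continuous variables, and Kruskal-Wallis tests for non-parametric data". No level is given for them. The section ends with the rule "Differences detected will be controlled for during the subsequent analyses".

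The Primary and secondary analysis section has a Cox model to "determine the effect of the interventions and adjust for any potential confounding variables", and for scale outcomes a "multivariable repeated measures analysis of covariance for continuous outcome variables" over the four data collection points. Neither sentence names a covariate.

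Elsewhere the article identifies variables that it regards as prognostic. Under Inclusion criteria, patients must "have at least one of the following risk factors for readmissions", followed by eight items that include age 75 or over, admission in the previous six months, multiple comorbidity, functional impairment and history of depression. None of these is committed to any model.

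**The concern.** Allocation is random, so any baseline difference between groups is due to chance, and the null hypothesis of the baseline test is known to be true. Its p-value carries no information on whether a variable predicts readmission. A rule built on it adjusts for whatever happens to fall below the threshold, prognostic or not, and leaves out strong predictors that happen to be balanced.

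Three things are at stake. Power that fixed adjustment would give is lost. The test no longer runs exactly at its stated level, because the model is chosen from the same data. And the hazard ratio is non-collapsible: the effect being estimated changes with the covariates in the model, so here its meaning is settled by chance imbalance.

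This is not detail that a condensed article leaves to an analysis plan. The article itself fixes the rule, and a later plan would have to contradict it.

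**Working it through.** **Inputs from the article.** Four groups, with 82 recruited and 62 completing per group (Sample size). The arithmetic there holds: 82 − 20 = 62 and 4 × 82 = 328. Inflating exactly gives 62/0.75 = 82.7. The 62 itself cannot be reproduced because no control median is given. It serves here only as the group size for the simulations.

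**Assumptions not in the article.** Baseline tests at 0.05; independent candidate variables; the covariate strengths shown below; for Cox, a control median of 8 weeks with censoring at 24 weeks.

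**Number of candidates.** Socio-demographic Information lists 8 items. Of the 8 eligibility risk factors, age and living alone are already among them, so 8 + 6 = 14. Adding the six named outcome scales, assessed at baseline, gives 20. The range used is 8 to 20.

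**Chance selection.** P(at least one p < 0.05) = 1 − 0.95^k:
- k = 8: 0.34
- k = 14: 0.51, with 14 × 0.05 = 0.7 false positives expected
- k = 20: 0.64

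Any particular variable enters with probability 0.05 (simulated 0.048 to 0.053), so a strong predictor is left out about 95% of the time. The chance that none of three named predictors enters is 0.95^3 = 0.86.

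**Cox power.** Simulation with 4 × 62 patients and 14 baseline variables, three of them prognostic. The true conditional hazard ratio is 8/12 = 0.667, that is, a 4-week difference on an 8-week median. Each cell shows pairwise power, then the mean estimated hazard ratio.

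| log-HR per SD | Unadjusted | Rule | Fixed covariates |
|---|---|---|---|
| 0.3 | 0.42; 0.700 | 0.42; 0.697 | 0.52; 0.663 |
| 0.5 | 0.31; 0.738 | 0.31; 0.734 | 0.50; 0.663 |
| 0.7 | 0.23; 0.776 | 0.23; 0.771 | 0.48; 0.663 |

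The rule performs almost exactly like no adjustment. The loss arises because omitting prognostic covariates pulls the hazard ratio towards 1.

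**Linear-model power.** Same layout, with the effect set for 90% unadjusted power. When three covariates explain 20%, 40% or 60% of variance, fixed adjustment gives 0.945, 0.986 and 0.998, and the rule gives 0.897, 0.903 and 0.908. With no prognostic covariates the three analyses agree (0.896 to 0.899).

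**Type I error under the rule.**
- Linear, 82 per group, one covariate: about 0.047 at r = 0.3, 0.044 at r = 0.5, and 0.036 to 0.038 at r = 0.7.
- Linear, 62 per group, 14 candidates, 40% to 60% of variance explained: 0.041 to 0.045 pairwise and 0.037 to 0.044 for the 3-df test.
- Cox, strong covariates, 8,000 runs: 0.047 to 0.048 pairwise and 0.039 to 0.044 for the 3-df test.
- Fixed covariates: about 0.05 (0.046 to 0.058 across runs, including Monte Carlo error).

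**The case against.** The strongest reply is that little is broken. The planned log-rank comparison does not depend on covariate choice. The Cox clause on potential confounders carries no significance condition and could admit age, previous admission or comorbidity. For scale outcomes, baseline is one of the four time points, so the covariate likeliest to be strongly correlated with outcome is already in the model.

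Most of this stands, and it limits the point. It is too strong to say that the plan excludes the known predictors: the rule omits them about 95% of the time, but the Cox clause leaves a second way in. That clause names nothing, however, so it adds post hoc choice rather than closing it. The log-rank test keeps its level but uses no covariates, so it recovers none of the forgone power. The point about scale outcomes is fair, and the gap is clearest for time to readmission, the endpoint behind the sample size.

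A reader might infer that the rule inflates false positives. The figures show the reverse: the error rate is slightly low. Only if the better of the unadjusted and rule-adjusted Cox results were taken does pairwise error reach 0.055 to 0.060, and the article does not propose that.

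A reader might also apply the variance factor 1/(1 − r²), which is 1.33 at r = 0.5 and 1.96 at r = 0.7, to the readmission endpoint. It holds for linear models only.

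Nor do the Cox powers near 0.5 show that the trial is undersized. They follow from the assumed 8-week median, and only the contrast between columns is informative.

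**Conclusion.** The concern holds as a badly fixed covariate rule. It does not invalidate the primary comparison, but it should be changed. The main cost is forgone power in the Cox analysis: about 0.10, 0.19 and 0.25 in absolute terms (0.52 − 0.42, 0.50 − 0.31, 0.48 − 0.23) as covariate strength rises from 0.3 to 0.7 log-HR per SD. A mildly conservative Type I error, and a hazard ratio whose meaning depends on chance imbalance, are secondary.

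The sizes rest on the assumed test level, candidate count, independence, covariate strengths and control median. The direction of the power difference was the same for every prognostic strength tried. That the rule selects by chance follows from randomisation alone and needs none of the assumed covariate strengths or the control median.

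**What to change.** Delete the sentence that ties adjustment to detected baseline differences, and the open-ended confounder clause in the Cox sentence. Present baseline data descriptively, without tests.

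Before analysis, name a short fixed covariate set for the Cox and repeated-measures models, to be used whatever the observed balance. Candidates are hospital, age, admission in the previous six months, multiple comorbidity as recorded, and baseline functional status. For scale outcomes, keep the scale's own baseline in the model. The article says that data collection was still under way, so this could be settled before analysis.

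One check is needed first. Eligibility requires only one risk factor and treats comorbidity as two or more conditions, so the article does not show that every factor, or a comorbidity count, is recorded for every participant. The list should be confined to what is recorded for all.

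The cost is about two sentences of text, a few degrees of freedom, and a hazard ratio to be read as conditional on the named covariates.
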